### Comparator and intervention

Recruited ED physicians will be allocated into the control and intervention groups based on their starting posting date in the ED (e.g., 2^nd^ quarter, 3^rd^ quarter etc). Fig 1 illustrates the flowchart and timeline for the respective groups involved in the study.

**Fig 1 pone.0336801.g001:**
[figure not shown]
Flow chart and timeline of the study.

In the first phase for both groups, ED physicians will follow the usual clinical practice (“Do nothing”) of making imaging referrals without consulting CDSS. Both groups will be informed during their onboarding on the availability of imaging referral guidelines in the training handbook and also on the intranet. Specifically, the physicians in the control group will not receive any CDSS introduction/orientation and no additional imaging referral guidelines education beyond the standard onboarding process. Simultaneously, a retrospective analysis of the electronic medical records will be performed.

The study included consecutive patients referred to the ED’s radiology department for cervical and lumbar spine radiography by the cohort of recruited ED physicians. Patients who had imaging referrals from general practitioners will be omitted due to our lack of access to the clinical notes for this particular cohort. For each case, the initial clinical diagnosis (reasons for the referral), the ordered procedure, patient demographics (age and gender), and ED clinical notes will be collected. To enhance the accuracy of analysing each imaging referral, the initial clinical diagnosis will be integrated with the corresponding ED clinical notes, including signs, symptoms, clinical examination, and red flags. This integration will result in a more comprehensive “indication(s)” for the imaging procedure. The appropriateness of each imaging referral will be determined with reference to localised and institutional approved imaging referral guidelines built on imaging referral guidelines published by ACR, ESR and RCR (Refer to Table 1). The records will be archived to REDCap (Research Electronic Data Capture) hosted by SingHealth for subsequent analysis.

**Table 1 pone.0336801.t001:** Imaging referral guidelines* for X-ray Cervical and Lumbar Spine.

Procedure	Clinical condition	Appropriate Imaging Criteria
X-ray Cervical Spine	Acute trauma	1. Patient age is > 65 years old 2. Patient GCS score <15 3. Patient is intoxicated 4. Patient has midline spinal tenderness 5. Presence of focal neurological deficit 6. Presence of paraesthesia in extremities 7. Patient is unable to actively rotate neck left and right to 45 degrees 8. Not possible to test range of neck movement during patient assessment 9. Presence of dangerous mechanism of injury – fall from >1 meter/5 stairs 10. Presence of dangerous mechanism of injury – axial load injury 11. Presence of dangerous mechanism of injury – high speed motor vehicle accident 12. Presence of dangerous mechanism of injury – rollover motor vehicle accident 13. Presence of dangerous mechanism of injury – motor vehicle accident with ejection 14. Presence of dangerous mechanism of injury – motorised recreational vehicles 15. Presence of dangerous mechanism of injury – bicycle collisions
	Non-traumatic neck pain	1. Patient has history and/or current malignancy 2. Patient has prior cervical spine surgery 3. Presence of symptoms for spinal cord injury 4. Patient is suspected to have an infection 5. Patient has history of IV drug use 6. Patient has systemic disease including spondyloarthritis and diffuse idiopathic skeletal hyperostosis 7. Presence of intractable pain despite therapy 8. Patient has tenderness to palpation over a vertebral body 9. Presence of neurological deficits 10. Presence of radiculopathy 11. Presence of neck pain
X-ray Lumbar Spine	Low back pain (LBP)	1. Patient age is > 65 years old 2. Patient is osteoporotic 3. Patient has chronic steroid use 4. Patient has low velocity trauma 5. Patient is suspected to have metastatic disease 6. Patient is suspected to have an infection 7. Patient is immunosuppressed 8. Patient is a surgical candidate with persistent or progressive symptoms during or following 6 weeks of conservative management 9. Patient has prior lumbar surgery with new or progressive symptoms or clinical findings 10. Patient has trauma of dangerous mechanism

*Approved by Institution’s Medical Board.

During the second phase of the study, the ED physicians in the control group will continue their usual clinical practice of ordering imaging without consulting CDSS (“Do nothing”). We will study the referral practices of the ED physicians in the control group over a consecutive period of two months, using a pragmatic approach. We will perform a retrospective analysis of the electronic medical records, following the same approach as in Phase 1.

Conversely, the ED physicians in the intervention group will receive individual access to a CDSS after a two-month period (Phase 1 – No CDSS intervention), and they will continue clinical practice using the standalone CDSS, which will incorporate localised and approved institutional imaging referral guidelines. The CDSS adopted in this study will be xWave CDS (xWave Technologies Ltd., Dublin, Ireland), which is a cloud-based Software as a Service (SaaS) platform with ISO27001 certification and developed in partnership with both the ESR iGuide and RCR iRefer. xWave CDS is fully hosted in Amazon Web Services (AWS) (Seattle, USA), and access is through the public internet. There is no hardware required onsite other than devices to access a web browser. Approval will be sought from the local hospital information technology team to whitelist the xWave CDS uniform resource locator (URL) for use by physicians on the hospital computer system. As the CDSS is not integrated into the Computerised Provider Order Entry (CPOE) ordering process, physicians will be required to toggle between the CPOE platform and xWave CDS. Modifications will be made to the xWave CDS user interface to incorporate elements that were deemed user-friendly as highlighted by local ED physicians during a previous focus group study [40]. This includes consolidating imaging referral guidelines onto a single page and replacing drop-down boxes with checked boxes.

Briefing slides and an introduction/orientation to the CDSS will be provided to ED physicians utilising the CDSS prior to the start of this second phase (Phase 2). The briefing slides will be curated by the vendor project manager and the principal investigator (PI) and subsequently be reviewed by the senior ED physicians for comprehensibility to ensure that the materials are well-defined and well-understood. Similarly, both the project manager and the PI will blueprint a 15-minute content plan for the introduction/orientation. The introduction/orientation will be conducted virtually by the research team members and the project manager assigned to the implementation. Topics covered include: (1) introduction to CDSS; (2) user workflow; (3) orientation of the CDSS input screen; (4) orientation of the CDSS guidelines screen; and (5) orientation of the CDSS recommendation screen. There will be no evaluation at the end of the introduction/orientation, but time will be dedicated for questions and answers. While no criteria for physician learning are available, it was deemed that the most effective learning for the time-constrained physicians was self-directed through the curated briefing slides, which will be disseminated through email and WhatsApp group.

The physicians will select pre-defined clinical history from the CDSS for imaging recommendations, and they will have the option to either follow or disregard them. We will study the referral practices of the recruited ED physicians in the intervention group over a consecutive period of two months. While ED physicians are not constricted by guidelines, during the study’s second phase, there will be special strategies to improve compliance and to motivate the physicians to adhere to the guidelines. This includes email reminders and the emphasis on the audit process.

The evaluation process in Phase 2 will mimic the pre-implementation evaluation process (Phase 1) to ensure comparable results and data. Essentially, we want to conduct a careful review of the difference between the baseline and post-implementation results. The analysis will include all participating physicians in an intention-to-treat fashion.

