### Characteristics of participants

A purposive sample of junior ED physicians will be approached via the ED Trauma lead. Inclusion criteria will include non-specialist EM physicians, and exclusion criteria will include non-specialist ED physicians who are unable to commit to the study period of 4 months (i.e., rotating/posting out of the ED within the study timeframe). Only non-specialists ED physicians will be recruited as they are the primary care providers for most of the ED patients and also account for the majority of the X-ray imaging referrals from the ED. Additionally, they are mostly assigned for clinical duty in the P3 and P4 sections of the ED (patient acuity category status P3: ambulant patients with minor emergencies and P4: non-emergency cases), where a substantial volume of X-ray cervical and lumbar spine are requested [38]. Notably, a previously conducted study in the same ED revealed that non-specialists accounted for a greater proportion of inappropriate orders as compared to specialists [22]. Consequently, this navigated us from the pitfall of recruiting physicians with a low baseline percentage of inappropriate imaging requests, which limits the potential for reduction [39].

This study will not employ randomisation or blinding due to its pragmatic design. The research team will take informed consent verbally prior to the study’s commencement, following an introduction and briefing.

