#### Outcome 1: Adherence to evidence-based imaging guidelines.

The primary goal is to determine the impact of the CDSS on adherence to evidence-based imaging guidelines in terms of the appropriateness rates of imaging for cervical and lumbar spine X-rays.

For both groups (“Do nothing” and CDSS), we will compare pre-implementation data on the appropriateness of spine imaging referrals with post-implementation data of the same duration (2 months). Multiple readers will evaluate each clinical indication for appropriateness using the local set of diagnostic imaging referral guidelines, with disagreement resolved by consensus.

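### The article describes appropriateness scoring phase by phase, so a shift in how readers apply the criteria cannot be excluded from the primary pre/post comparison

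*Protocol article*

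**What the plan says.** Under Comparator and intervention, the article sets the record review for Phase 1 alongside that phase: "Simultaneously, a retrospective analysis of the electronic medical records will be performed". For the control group in Phase 2 it states: "We will perform a retrospective analysis of the electronic medical records, following the same approach as in Phase 1". For Phase 2 evaluation in general it says: "The evaluation process in Phase 2 will mimic the pre-implementation evaluation process (Phase 1) to ensure comparable results and data".

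Two elements leave the timing less definite. The Phase 1 review is itself called retrospective, and the same section says of the records: "The records will be archived to REDCap (Research Electronic Data Capture) hosted by SingHealth for subsequent analysis".

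Outcome 1 describes the scoring: "Multiple readers will evaluate each clinical indication for appropriateness using the local set of diagnostic imaging referral guidelines, with disagreement resolved by consensus". Characteristics of participants says: "This study will not employ randomisation or blinding due to its pragmatic design". Physicians are "allocated into the control and intervention groups based on their starting posting date in the ED", with calendar quarters given as the example.

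Under Data and statistical analysis, the primary test is a paired t-test of each physician's change in mean appropriateness between phases. A patient-level multilevel logistic model with a phase-by-arm interaction complements it, and both sets of estimates are to be reported side by side.

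**The concern.** The natural reading is two evaluation rounds, with Phase 1 records read first and Phase 2 records later. Scoring order would then coincide with phase order.

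Applying Table 1 is partly a matter of judgement. Readers merge the referral reason with the ED notes into a composite indication, then decide whether, for example, infection or metastatic disease was suspected, or pain was intractable. How borderline cases were settled early on can influence how similar cases are read later.

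This is an effect of order as well as of knowledge. Readers masked to phase could still drift if every Phase 1 record came before every Phase 2 record. The primary test compares exactly these two sets of scores within physician, and pairing gives no protection because drift follows phase. Drift towards scoring records as appropriate would look like a CDSS benefit; drift the other way would hide one.

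**Working it through.** **1. The plan's own figure.** Sample size gives power 0.9, alpha 0.05, effect size 0.3 and 468 in total, 235 per group.
- Two-sided normal formula: n = 2 × (1.960 + 1.282)² / 0.3² = 233.5, so 234 per group and 468 in total.
- The t-based version for independent groups gives 234.5, so 235 per group.

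The stated figure reproduces, and nothing in this point changes it.

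**2. The planned effect in percentage points.** With the article's 20% inappropriate, the SD of a binary outcome is √(0.2 × 0.8) = 0.4. An effect of 0.3 SD is 0.3 × 0.4 = 0.12, or 12 points.

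**3. Illustration of drift.** The article gives no drift rate, so this input is assumed. Suppose there is no CDSS effect, 235 independent X-rays per phase, and a second round that re-calls 10%, 15% or 25% of the inappropriate X-rays as appropriate. The scored rate then moves by 0.20 × 0.10 = 2 points, 0.20 × 0.15 = 3 points, or 0.20 × 0.25 = 5 points.

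With p1 = 0.20 and p2 = 0.20 − d:

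z = d / √[p1(1 − p1)/235 + p2(1 − p2)/235]

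P(reject) = Φ(z − 1.96) + Φ(−z − 1.96)

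| Drift d | p2 | z | P(reject) | Share of 12 points |
|---|---|---|---|---|
| 2 points | 0.18 | 0.55 | 0.086 | 17% |
| 3 points | 0.17 | 0.84 | 0.134 | 25% |
| 5 points | 0.15 | 1.43 | 0.298 | 42% |

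Without drift the rejection rate is 0.05.

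**4. From the illustration to the planned test.** The planned test works on physician-level changes, and the article gives no number of physicians, so its false-positive rate cannot be computed. The bias in the estimate does not depend on that number: drift of d points that is common across physicians shifts the mean within-physician change by d.

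**5. What the control group removes.** On the risk-difference scale, the bias in the difference-in-differences is drift in the intervention arm minus drift in the control arm.
- 3 points in each arm: 3 − 3 = 0.
- 3 points in the intervention arm only: 3 − 0 = 3 points in favour of the CDSS.
- 3 points in the control arm only: 0 − 3 = 3 points against it.

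Status and timeline runs data collection from 1 May to 30 November 2025, seven months, while each physician is followed for four. That fits arms staggered by about a quarter, though the article does not say so outright. If readers adjust most in the early batches, drift would be larger in whichever arm was read first.

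**The case against.** **Timing is inferred.** The review is called retrospective, records are archived for later analysis, and Status and timeline separates the end of data collection from the end of analysis. All of this also fits extraction during each phase with scoring afterwards. This objection stands in part: phase-order scoring is the more natural reading but not a settled fact. If later scoring is intended, the Phase 1 sentence needs correcting.

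**No calibration step is described.** A reader might infer that readers recalibrate between the phases and that drift is therefore built into the effect. The article does not support this. Its only mention of consensus is "with disagreement resolved by consensus", which settles individual cases. Drift is possible, not certain.

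**The criteria are fixed and many are objective.** Table 1 is a board-approved list. Age over 65, GCS below 15, previous spine surgery and long-term steroid use leave little room for interpretation, and several readers limit the drift of any one. This reduces the likely size of the problem but does not remove it for the judgement-based items.

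**There is a control group.** It is scored in the same way, and the interaction removes drift common to both arms. That holds on the scale where the drift is equal. However, the interaction belongs to the complementary model, and the Limitations section itself concedes that the two groups are not directly compared.

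**The false-positive rates are not those of the planned test.** This is correct. They assume one-directional drift of an assumed size and independent X-rays, and serve only as an illustration.

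**A condensed article may leave reading order to a fuller document.** That would answer mere silence. Here the text does describe a workflow, and it points towards phase-by-phase scoring.

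**Conclusion.** The concern holds as a risk that the described workflow leaves open. The text points to scoring by phase, provides no masking of readers, and relies on a primary pre/post test with no internal protection against a change in how the criteria are read. The phase-by-arm interaction protects only against drift that is equal in both arms.

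The size and direction of drift are unknown. Under the stated assumptions, 2 to 5 points of drift equals 17% to 42% of the 12-point planned effect, with an illustrative false-positive rate of about 9% to 30%. The documents do not support the conclusion that drift will occur, or that it would favour the CDSS. The change is worth making because it is cheap and protects the primary outcome; the concern does not by itself invalidate the design.

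**What to change.** Extract and archive records during each phase as planned, but state that appropriateness will be scored only after both phases of both arms are collected. Score all records in one computer-generated random order that mixes phase, arm and calendar date, with phase and arm labels hidden from readers where feasible. Reword the Phase 1 sentence so that it refers to extraction and not to scoring.

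If scoring must begin earlier, put a random subset of Phase 1 records back into the later batches, unmarked, and compare their first and second scores to check for drift.

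No extra readers or patients are needed. The cost of the first option is that scoring is compressed into the month between the end of data collection (30 November 2025) and the end of analysis (31 December 2025). The cost of the second is that a small subset is scored twice.

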#### Outcome 2: Clinical effectiveness.

Addressing clinical effectiveness is critical to answering the question, “What is the impact of CDSS on patient outcome(s)?”. To assess the clinical effectiveness of CDSS in the real world, we will examine the clinically significant positive rates of imaging procedures performed, in tandem with the subsequent patient dispositions (i.e., treated and discharge, admission, referral to specialist, referral to physiotherapy and “At Own Risk”) at the end of the individual patient journey in the ED. The radiological reports of associated imaging procedures will be evaluated for significant positive findings that will impact therapeutic decisions, such as fractures in both the cervical and lumbar spines and soft tissue swelling in the cervical spine (i.e., fracture or prevertebral soft tissue swelling – sign of cervical spine jury, were considered positive; all else considered negative). To facilitate comparison in the proportions of positive findings among the categories, we will assess the imaging positivity rates in both the appropriate and inappropriate imaging cohorts. By using a longitudinal approach to monitor patients until their disposition, we will be able to clarify the risks physicians face regarding patient safety and quality of care, particularly in relation to the question: “What impact will following or not following imaging recommendations from the guidelines have on patient outcomes?” [41].

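### Appropriateness is scored retrospectively from the ED notes without masking readers to the X-ray result, so the Outcome 2 comparison of positivity by appropriateness is open to incorporation bias

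*Protocol article*

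**What the plan says.** The scoring rule is in the Methods, under Comparator and intervention (text after Fig 1). During Phase 1, "a retrospective analysis of the electronic medical records will be performed". For each case "the initial clinical diagnosis will be integrated with the corresponding ED clinical notes, including signs, symptoms, clinical examination, and red flags", and "This integration will result in a more comprehensive “indication(s)” for the imaging procedure". Each referral is then judged against the criteria in Table 1. The control group's second phase follows the same approach, and for Phase 2 generally "The evaluation process in Phase 2 will mimic the pre-implementation evaluation process (Phase 1) to ensure comparable results and data".

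Under Outcome 1, "Multiple readers will evaluate each clinical indication for appropriateness using the local set of diagnostic imaging referral guidelines, with disagreement resolved by consensus". Under Characteristics of participants, "This study will not employ randomisation or blinding due to its pragmatic design".

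Under Outcome 2, radiology reports are evaluated for significant positive findings and "we will assess the imaging positivity rates in both the appropriate and inappropriate imaging cohorts". The same section follows patients to disposition and says that "we will be able to clarify the risks physicians face regarding patient safety and quality of care".

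**The concern.** A comparison of film positivity between appropriate and inappropriate referrals is interpretable only if the classification was made independently of the film result. The article does not secure that. When a case is scored, the visit is over and the record may contain text written after the film was read. Consensus between readers settles disagreement, but it does not help if all readers know the result.

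Once a fracture is known, a note may record a criterion more fully, or a reader may more readily accept one as met. A positive film would then tend to leave the inappropriate class. Positivity there would look lower than it is, and omitting films that the guideline does not support would look safer than the data warrant. This can arise within every phase and group, so it is a different matter from readers knowing the phase or group.

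**Working it through.** **Inputs from the article.** Sample size: 20% inappropriate, power 0.9, alpha 0.05, effect size 0.3, 468 in total, 235 per group. Introduction: 36.2% inappropriate in an earlier local lumbar study. The article gives neither the positivity nor the share of films that might be re-scored; both are assumptions below.

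**The plan's own figure.** A two-sided comparison of two independent means with effect size 0.3 needs 2(1.960 + 1.282)²/0.3² = 233.5, so 234 per group and 468 in total. The t-test version gives 234.46, so 235 per group (470 in total). Both stated figures reproduce. I use 470 films only as a yardstick: patients are enrolled consecutively and the number of films is not fixed.

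**Model.** Let p be the share inappropriate, q the true positivity (equal in both classes, so the true ratio is 1.0), and u the share of positive inappropriate films scored appropriate because of the result.

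- Observed positivity, inappropriate: q(1 − u)/(1 − qu)
- Observed positivity, appropriate: [q(1 − p) + pqu]/[(1 − p) + pqu]
- Observed share inappropriate: p(1 − qu)

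The number of films cancels from all three. The number of films moved is 470pqu.

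| p | q (assumed) | u (assumed) | Inappropriate | Appropriate | Ratio | Films moved of 470 |
|---|---|---|---|---|---|---|
| 20% | 3% | 25% | 2.27% | 3.18% | 1.40 | 0.7 |
| 20% | 3% | 50% | 1.52% | 3.36% | 2.21 | 1.4 |
| 20% | 5% | 25% | 3.80% | 5.30% | 1.39 | 1.2 |
| 20% | 5% | 50% | 2.56% | 5.59% | 2.18 | 2.4 |
| 36.2% | 3% | 50% | 1.52% | 3.82% | 2.51 | 2.6 |
| 36.2% | 5% | 50% | 2.56% | 6.33% | 2.47 | 4.3 |

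For the second row: 0.03 × 0.5/(1 − 0.015) = 1.52%; (0.024 + 0.003)/(0.8 + 0.003) = 3.36%; ratio 2.21.

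**Fragility.** At p = 20%, 470 films include 94 inappropriate ones. At 2% to 5% positivity these hold 94 × 0.02 = 1.9 to 94 × 0.05 = 4.7 positives, so very few films drive the ratio.

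**Direction.** The model moves positives only, so its direction is built in. If late entries also moved the same share u of negative inappropriate films, positivity in both classes would stay at q and the ratio at 1.0. The bias depends on positives moving more readily than negatives.

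**Primary outcome.** With only positive films moving, the share inappropriate becomes 0.20 × (1 − 0.05 × 0.5) = 19.5%. In the extreme case of 10% positivity with all positives moved, it is 0.20 × (1 − 0.10) = 18.0%.

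**Which films can move.** Table 1 does not say how its criteria combine; I read any one as sufficient. Age over 65 cannot shift. In non-traumatic neck pain, neck pain itself is listed as a criterion, so almost every such film is already appropriate. That leaves cervical trauma (midline tenderness, neurological deficit, mechanism) and lumbar films (for example osteoporosis, low-velocity or dangerous trauma, suspected metastatic disease, suspected infection).

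**The case against.** The strongest reply is that this is a condensed article, and that limits on note entries and masking of readers may stand in a full protocol that is not shown. Some of the text also points towards separation. The case data listed for scoring are the referral reason, procedure, demographics and ED notes, without the radiology report or disposition. The note content named is of the kind usually gathered before imaging. Readers evaluate the clinical indication, and reports appear as a separate source under Outcome 2. The no-blinding sentence stands under participant characteristics and does not mention readers.

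This narrows the route but does not close it. Merging the notes is a scoring rule that the article itself fixes. A result can be written inside an ED note, findings elicited early can be documented late, and the article nowhere protects the readers from the result.

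Four stronger readings are tempting, and the article does not support them:

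- That the whole note, including text written after the film, will be used and that readers will see the result. The article sets no cut-off, but it says neither of these things.
- That the bias must run one way. Late entries such as steroid use or prior surgery could also upgrade negative films.
- That one or two records decide the safety conclusion. Outcome 2 sets no test or threshold, and with so few positives it will be imprecise in any case.
- That the safety statement rests on this comparison alone. The sentence on risk is tied to following patients to disposition.

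**Conclusion.** The point holds as a weakness that the stated method permits, not as a bias shown to occur. The classification may be influenced by the result against which Outcome 2 then compares it. The probable effect is to lower positivity in the inappropriate class, mainly for cervical trauma and lumbar films. The ratios of about 1.4 to 2.5 are illustrations. They rest on assumed positivity of 3% to 5%, an assumed 25% to 50% of positive inappropriate films re-scored, and no movement of negative films. The true size cannot be derived from the article. Movement of positive films has little effect on the primary rate, and scoring is the same in both phases. This is a worthwhile, inexpensive improvement to Outcome 2; it does not undermine the primary analysis.

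**What to change.** Keep the merged-note score as the main classification, and add to the scoring rule under Comparator and intervention:

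1. Readers score appropriateness with the X-ray report, any result text within the notes, and the disposition withheld.
2. The score is locked before positivity is recorded.

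Under Outcome 2, add a sensitivity analysis that repeats the positivity comparison with a classification based only on the referral text and, where time-stamps allow, entries made at or before the order.

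I would not make the order-time score the main one. It would class films as inappropriate merely because findings elicited before the order were typed later, and so would alter the primary outcome to protect a secondary one.

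The cost is a little extra extraction work and one further analysis. Patient care does not change, because the records are reviewed retrospectively.
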